## Abstract

**Background:**

Working memory deficit is one of the most critical complex cognitive impairments in schizophrenia. Repetitive transcranial magnetic stimulation (rTMS) is an effective adjuvant therapy, but not still unsatisfactory. Intermittent theta burst stimulation (iTBS), which has recently been used in clinical practice, may have faster and stronger effects comparing the traditional model (10-Hz high-frequency rTMS). A large number of studies have showed that rTMS, especially iTBS, can enhance the neural plasticity of the brain, and cognitive training can improve the cognitive function of schizophrenia. Is there any facilitation effect of iTBS add on cognitive training (such as working memory training, WMT) on cognitive function enhancement in schizophrenia is still unknown.

**Methods/design:**

The proposed study is designed of a double-center, double-blinded, randomized controlled trial that will include 200 schizophrenia patients between 18 and 45 years of age. The patients will be randomized to four groups, i.e., the study group (iTBS+WMT), WMS control group (iTBS+ Simple Response Training (SRT)), iTBS control group (sham iTBS+WMT), and placebo control (sham iTBS+SRT). The patients will receive 3 min 20 s of real or sham stimulation, followed by a short 1–2-min rest and 40 min of WMT training or SRT immediately. Neuropsychological and clinical symptom assessments, with functional and structural MRI, will be performed on baseline, post-treatment, and 3- and 6-month follow-up periods. The primary outcome is cognitive function measured by the MATRICS Consensus Cognitive Battery (MCCB). The secondary outcomes are changes in neuroplasticity, as measured by MRI and other behavioral assessments.

**Discussion:**

The aim of our study is to explore the facilitation effects of iTBS added on WMT in improving cognitive function of schizophrenia. That means, patients with schizophrenia will benefit more in cognitive function improvement from the combination training mode of “preheating (iTBS stimulation changes the neural activity of working memory-related brain regions) and ironning (working memory training).” And the long-term effects of this combined training model will be assessed at a 6-month follow-up period. In case of a significant improvement of working memory with a prolonged effect, the iTBS combined with WMT protocol could be considered as a first-line clinical protocol in schizophrenia treatment. More broadly, the potential for increased universality and efficiency of rTMS with the iTBS model to enhance the neural plasticity of the brain should have a more positive effect on cognitive function in schizophrenia.

**Trial registration:**

chictr.org.cn ChiCTR1900023405. Registered on 25 May 2019

## Background

Schizophrenia is one of the most common severe mental disorders which can seriously affect human health all over the world. The lifetime prevalence rate of schizophrenia is 7.81‰ in China, leading to serious deficiencies or loss of social functions and general life and working skills [1]. This disorder not only causes mental disability, but also brings heavy mental and economic burden of patients, families, and society. Among the causes for disability, cognitive deficit (CD) is one of the most important ones, which has a serious impact on patients’ daily life, work, and disease outcomes [2].

The cognitive impairment of patients with schizophrenia is complicated, among which working memory (WM) deficit is one of the most core and critical cognitive impairments suffered by these patients [3]. Studies have confirmed that central control components play a critical role in working memory system, which are mainly related to dorsolateral prefrontal cortex (DLPFC) function. Meanwhile, the basal ganglia and hippocampus are also involved in working memory processing [4, 5]. The abnormal functional connection between the prefrontal lobe and other working memory-relevant areas may be a vital neurological basis for the deficit of working memory in schizophrenia [6, 7]. MRI shows that the thickness of the left DLPFC cortex and the volume of gray matter decreased in schizophrenic patients [8], and the volume of gray matter decreased in the prefrontal lobe [9] was significantly correlated with the performance of working memory. In addition, diffusion-weighted imaging (DTI) reveals impaired white matter in uncinate fasciculus, the main area of frontotemporal junction in schizophrenic patients, which is significantly correlated with impaired working memory and daily function [10].

Large-scale multi-center trials have shown that cognitive deficits in schizophrenia patients can be improved by repeated intensive and targeted cognitive training, such as cognitive remediation therapy (CRT) [11, 12]. Although a mass of research has confirmed that cognitive remediation therapy and other neuropsychological trainings can significantly improve the cognitive function of schizophrenia patients, the overall effect value is about 0.4, which amounts to a moderate effect level, especially for working memory, which is the core basic cognitive deficit. The improvement effect is lower than that of general cognition, only about 0.35. The recent systematic review of the effects of cognitive training shows that the overall effect of cognitive training is 0.38 and the working memory effect is 0.29 in schizophrenia [13]. Hence, it can be seen that the clinical effect of cognitive training needs to be improved.

Numerous studies have shown that cognitive training plays a role by altering the brain structural and functional plasticity [14]. Brain structural plasticity includes improved cortical thickness [15] or increased white matter integrity [16]. And the functional plasticity includes brain functional changes [17] and cerebral blood flow [18]. So far, repetitive transcranial magnetic stimulation (rTMS) is deemed to be one of the most effective and safe non-drug methods to improve cerebral neural plasticity. It can change the activity of cortical nerve temporarily or continuously and enhance the neural plasticity. However, the recent results are inconsistent. A large sample, multi-center, randomized controlled study recently has found that rTMS at 10 Hz for three consecutive weeks can improve some aspects of cognitive performance, but there is no significant improvement compared with the Sham-stimulation group. It is suggested that the improvement of cognitive function by simple conventional rTMS is limited [19]. At the same time, the clinical conventional rTMS is relatively long-time, generally takes about 20–30 min each session, and the clinical efficiency on cognitive function is not clear, which limits its application on improving cognition of schizophrenia.

However, with regard to recent scientific literature, a newer form of rTMS called intermittent theta burst stimulation (iTBS) has been developed, which simulates burst discharges of physiological action potentials in the central nervous system by cluster stimulation. Compared with conventional rTMS, it can regulate the activity of potential regions in a shorter time and produce stronger and more lasting post-stimulation effects [20]. Theta burst stimulation (TBS), a new stimulation method based on repetitive stimulation, can better simulate the true action potential of human neurons. By regulating synaptic plasticity, TBS produces a rapid and efficient response to the human motor cortex. The major long-term forms of synaptic plasticity, referred to as long-term potentiation (LTP) and long-term depression (LTD), are induced by changes in the postsynaptic Ca2+ concentration [21]. Short bursts of iTBS stimulation, mimicking a common pattern of hippocampal pyramidal neuronal discharge, induce LTP in the hippocampus only when the stimulation is repeated at intervals less than 2 s [22]. And intermittent TBS, which denotes short trains of intermittent bursts, leads to the Ca2+ influx-related excitatory effect (through postsynaptic NMDA receptors) and produces the LTP-like effect [23]. There is less research about iTBS, a new model, compared with conventional rTMS in psychiatric disorder. A retrospective study conducted by Bakker in 2014 found that iTBS (expending 6 min) and conventional rTMS (expending 30 min) had similar effects on the dorsal prefrontal cortex [24]. In the RCT study with higher evidence intensity, Blumberger team has found that iTBS improved depression in patients with treatment-resistant depression and was not inferior to conventional 10-Hz rTMS, which was more efficient in time efficiency (4 min vs 37.5 min). Both treatments have lower shedding rates and similar side effects, with both good safety and tolerability [25].

Although rTMS improves the neuroplasticity of the brain, the improvement of cognitive function is frequently limited to some extent. It is necessary to combine other methods, such as cognitive training, to boost cognitive functions. A research about the combination of rTMS and motor rehabilitation has testified that the intervention based on improving cortical plasticity is more effective than other groups. However, a recent systematic review on the improvement of working memory in schizophrenia suggests that the combination of rTMS and working memory training (WMT) may improve the working memory ability [3].

So far, traditional cognitive training, especially working memory training, has small to medium effect on the improvement of cognitive function. Although standard rTMS can improve the neural plasticity, there are some limitations, such as inefficiency, time-consuming, and lack of strong evidence of cognition improvement. To sum up, we hypothesize that there is a joint enhancement effect of combination between iTBS and WMT, i.e., the combination training mode of “preheating (iTBS stimulation changes the activity of working memory-related brain regions) and ironning (working memory training).” At present, there is no relevant research report to explore whether and how the joint intervention will have a combined effect on improving cognitive function, especially working memory, in schizophrenic patients.

To our knowledge, this is the first study to test the efficacy of a combination of iTBS and WMT on working memory and other cognitive functions of schizophrenia using a double-blinded, randomized controlled trial design. In order to evaluate the efficacy of invention, we will use behavior outcomes (such as neuropsychological assessment) and neuroplasticity outcomes (such as brain microstructural index) combining with neuroimaging indexes. This study will provide scientific evidence for improving cognitive deficits, especially working memory deficits, and elucidate the neuroplasticity mechanism of iTBS stimulation combined with working memory training.

## Methods/design

### Study design

The study will be implemented as a double-center, double-blinded, randomized trial. This was registered under Chictr.org.cn (ChiCTR1900023405). This study will be reported in accordance with both the Consolidated Standards of Reporting Trials (CONSORT) statement and the CONSORT statement for non-pharmaceutical interventions [26, 27].

The primary objective is to explore the facilitation (enhancement) effects of iTBS-induced neuroplasticity changes on the direct and migration effects of working memory training on the cognitive function of schizophrenia. The secondary objectives are to investigate the effects of iTBS, working memory training on brain functional and structural plasticity in schizophrenia, and the facilitation (enhancement) of iTBS on brain functional and structural plasticity induced by working memory training.

### Participants

Two hundred patients with schizophrenia will be recruited on fulfillment of the inclusion criteria. The patients will be randomly allocated into four groups, i.e., the study group (iTBS+WMT), WMS control group (iTBS+ Simple Response Training, SRT), iTBS control group (sham iTBS+WMT), and placebo control (sham iTBS+SRT). Patients will be recruited in two specialty neurostimulation centers at Beijing Huilongguan Hospital, Shenyang Anning Hospital.

This trial has been approved by the local Ethics Committee and followed close to the principles of the Declaration of Helsinki (version 2004). And Standard Protocol Items: Recommendations For Interventional Trials (SPIRIT) Checklist is detailed in additional file according to requirements. All of the patients sign a written consent form in order to take part in the study, after acquainting the aim and procedures.

### Inclusion criteria

Conformity with the diagnostic criteria of schizophrenia in the fourth edition of the Diagnostic and Statistical Manual of Mental Disorders (DSM-IV) [28]Single item score of Positive And Negative Syndrome Scale (PANSS) positive scale was < 5; total score of PANSS positive scale was < 22Eighteen to 45 years of age and more than 5 years of formal educationVoluntarily participate in the study and sign consent formThe type and dosage of drugs not be adjusted in the past month and in the next monthCognitive impairment exists: the length of number backwards ≤ 6Right handedness determined by Edinburgh Handedness Assessment Scale

### Exclusion criteria

Patients with intellectual disability (ID) or neurocognitive disordersSevere recession or impulsive excitement, uncooperativeSevere depression, anxiety, and substance abuseHearing or visual perception disordersSevere physical diseases or side effects of medicine, unable to carry out cognitive trainingPregnant or lactating women

### Dropping criteria

Total ten sessions not to finish the training among four groupsThe relapse or aggravation of the disease needing the replacement of antipsychotic drugs

### Randomization

Participants will be randomly allocated to four groups: study group (iTBS+WMT), WMS control group (iTBS+SRT), iTBS control group (sham iTBS+WMT), and placebo control (sham iTBS+SRT) in a ratio of 1:1:1:1, with stratification. After patients have given their consent form, randomization will be performed by an independent and professional statistician who is blinded to the patient interventions using block randomization in R Programming (Mathsoft company, USA). Each center has its own enrollment time as a compatibility factor, and 8 patients in the vicinity of the enrollment time are used as a block. There are 15 blocks (total 120 patients) in Beijing Huilongguan Hospital and 10 blocks (total 80 patients) in Shenyang Anning Hospital. Then, the sealed randomization codes and intervention number are sent out to each hospital. Blinding will have to be broken only if a patient needs emergency handling. Once in this way, the participant will be managed as off-trial.

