### Blinding

Patients, research psychiatrists, radiologists, statisticians, and neuropsychologists who measure the primary and second outcomes will be blinded to the randomization status from beginning to end. Participants will not distinguish the group they belong to, will not have precise description of iTBS and training parameters, and will not be allowed to speak to each other. Meanwhile, blinding will be maintained for outcome assessment, data management, and analysis.

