### Sample size

The hypothesis is 77.2% response rate in the cognitive training group and 41.4% in the control group on our preliminary studies [32]. The difference between the two groups was improved about 35.8%, as the basis for calculation. With a statistical power of 80% and a significance level of 5%, the minimum sample size of 28 subjects is required in each group. With our previous research experience, we allow for a maximum dropout rate of 20%. The study adopts the block randomization to divide into groups with 8 patients in each block. The actual minimum sample size of each group was 34 cases. Combining each center clinical states, Beijing center inclusion number has been set to 120 patients to participate into this research and Shenyang center has 80 patients.

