## Trial status

Patient recruitment is currently ongoing. This is the first version of this protocol (V1.0). If the protocol needs to be amended, we should notify firstly the sponsor and the centers. After passing the ethics committee review, a copy of the revised protocol will be sent to the managers of two centers and be added to the web for record accurately. The first patient has been enrolled on December 23, 2019, and it is expected to finish by the end of 2020. Due to the impact of COVID-19, our related researches have been severely affected, and the end time will be appropriately postponed.

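### A single, published block size of 8 per centre could let an informed person foresee the end of a block; varied, undisclosed sizes without 4 would reduce this minor, conditional risk cheaply

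*Protocol article*

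**What the plan says.** The Randomization section of the protocol article allocates patients "in a ratio of 1:1:1:1, with stratification". It sets the block within each centre: "8 patients in the vicinity of the enrollment time are used as a block". It also gives the layout: "There are 15 blocks (total 120 patients) in Beijing Huilongguan Hospital and 10 blocks (total 80 patients) in Shenyang Anning Hospital". The Sample size section repeats the block size: "The study adopts the block randomization to divide into groups with 8 patients in each block".

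On procedure, the Randomization section says: "After patients have given their consent form, randomization will be performed by an independent and professional statistician who is blinded to the patient interventions". After that, "the sealed randomization codes and intervention number are sent out to each hospital".

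The Blinding section names those kept unaware: "Patients, research psychiatrists, radiologists, statisticians, and neuropsychologists who measure the primary and second outcomes will be blinded". Staff who operate the stimulator or supervise the training are not named. The Intervention section describes sham stimulation as a plastic model fixed on the real coil, and the control training as a simple key-press task in place of the memory task.

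The Trial status section reports: "Patient recruitment is currently ongoing".

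**The concern.** With one known block size and equal allocation, the content of each block is known in advance: two patients in each of four arms. Anyone who has kept count of the earlier allocations in the block can narrow down the remaining ones, and the last is fixed. The article makes the size available to anyone at the sites while patients are still being enrolled.

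The people best placed to keep count are those who deliver treatment. Over 30 sessions per patient they handle the coil with or without the spacer and start one of two different tasks, so they can probably tell the arm of the patients they treat.

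What would be at stake is allocation concealment. If a foreseen assignment affects which patient is approached next, or when, the arms may differ in prognosis in ways that baseline adjustment cannot fully remove. The real-versus-sham contrast deserves attention because the primary objective is whether iTBS enhances the effect of working memory training.

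**Working it through.** **The plan's own layout.** 15 × 8 = 120 and 10 × 8 = 80. That gives 25 blocks, 200 patients and 200 / 4 = 50 per arm. The stated layout is reproduced.

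**Inputs.** From the article: block size 8, four equal arms (so 2 per arm per block) and 25 blocks. Assumed for the upper bound: an observer who knows the block boundary and every earlier allocation in the block.

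**Certain assignments, four arms.**
- The 8th is always certain.
- The 7th is certain only if the last two share an arm. Given the arm of one of them, 1 of the other 7 places holds its partner, so the probability is 1/7 = 0.143.
- The 6th and earlier are never certain, because three remaining places cannot all belong to an arm with only two.
- Sum: 1 + 0.143 = 1.143 per block; × 25 = 28.6 of 200 (14.3%).

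**Best guess, four arms.** The observer always names an arm with the most places left. By exact enumeration, the chance of being right at positions 1 to 8 is 0.250, 0.286, 0.333, 0.400, 0.443, 0.476, 0.571 and 1. The sum is 3.76 of 8, or 47.0%, against 25% by chance.

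**Real versus sham only (4 + 4 per block).**
- 8th: always certain.
- 7th: 3/7 = 0.429.
- 6th: 3/7 × 2/6 = 0.143.
- 5th: 3/7 × 2/6 × 1/5 = 0.029.
- Sum: 1.60 per block; × 25 = 40 of 200.
- Best guess by enumeration: 5.33 of 8, or 66.6%, against 50% by chance.

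**Lower bound.** An observer with no knowledge of earlier allocations gains nothing from the block size: 0 certain, 25% guessing. The same holds for enrolment if all eight patients in a block have consented before any of them is randomized.

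**Effect of varying the size.** 400 simulated trials with centres of 120 and 80, four arms. The observer knows the earlier allocations and the set of sizes, but not the size of the current block.

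| Block sizes | Certain of 200 | Best guess correct of 200 |
|---|---|---|
| 8 only | 28.6 | 93.6 (47%) |
| 4, 8 | 14.8 | 97.1 (49%) |
| 4, 8, 12 | 6.9 | 92.0 (46%) |
| 8, 12, 16 | 4.7 | 86.9 (43%) |

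The row for 8 only agrees with the exact values (28.6 certain; 3.76 × 25 = 94.0 correct). Mixes that include 4 reduce certainty but hardly change guessing, because a block of 4 is itself easy to guess (2.08 of 4, or 52%). Leaving out 4 improves both measures.

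**The case against.** A reader might infer that the delivering staff see every allocation and that concealment is therefore broken. The documents do not support this. Nowhere do they say that one operator treats all patients at a centre, that operators know where a block starts, that they take part in enrolment, or that they pass allocations to those who enrol. That they recognise the arm of their own patients is a reasonable inference from the spacer and the two tasks, but it is not stated.

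There are also real safeguards. The research psychiatrists are blinded throughout, the codes are sealed, and an independent statistician randomizes after consent. The Randomization section can be read as randomizing a group of eight consented patients together, in which case the end of a block cannot steer enrolment. How codes are opened and who enrols are details that an article may leave to the full protocol, so their absence is not a fault.

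Most of this stands, and it limits the point to a conditional one. What remains is that sealing a code does not hide it from someone who can deduce it. Randomizing after consent also does not prevent a foreseen assignment from affecting who is approached. The fixed size is a stated rule and not an omission.

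**Conclusion.** The point holds as a minor, conditional improvement. It is neither an error nor a contradiction in the plan. The single block size, its publication during recruitment, the dispatch of codes to the hospitals and the absence of delivering staff from the blinded list are all in the article. The harm depends on one further condition that the article neither states nor excludes: that someone who knows the earlier allocations in a block can influence who is enrolled or when.

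The size therefore runs from 0 to about 29 of 200 certain four-arm assignments, and from 25% to 47% correct guessing. For real versus sham alone the upper bounds are about 40 of 200 and 67%. The upper ends assume a fully informed observer in all 25 blocks. Blocks already filled cannot be changed, so a remedy reaches only those still to come.

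**What to change.** For blocks not yet issued, the independent statistician should:

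1. Generate randomly varied block sizes within each centre, leaving out 4. With 8, 12 and 16, certain assignments fall from about 29 to about 5 per 200, and best guessing from about 47% to about 43%.
2. Keep the list and the sizes away from the sites and unpublished until recruitment closes.
3. Release each assignment singly, after consent and baseline assessment, in place of sending the sealed series to the hospitals. Randomization after consent is already in the plan; the single release and the baseline condition are new.

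Varying sizes lowers guessing only modestly, so the second and third steps matter at least as much.

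The cost is a short amendment, a regenerated list for the remaining patients, and possibly a small imbalance if the last block in a centre is incomplete. With a largest block of 16 (4 per arm), two arms can differ by at most 4 patients per centre. If the sponsor already randomizes each group of eight together after all have consented, a sentence saying so would answer the concern for the end of the block.

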### Data monitoring

The project management group is composed of [name] and [name]. The group is mainly responsible for managing the overall work of the two centers and reviewing every 6 weeks. The trial auditing group is composed of two staff members of the audit department and is responsible for regularly reviewing the progress, authenticity, and safety every 6 weeks. [name] is independently responsible for all data monitoring of the study. The intervention may produce mild adverse events, such as headache and irritability, which can be improved by giving the patient rest or interval stimulation. If the patients show unbearable, they can opt out of the trial. We should report this situation to the supervisory department for record. The trial auditing group and the independent Data Monitoring and Ethics Committee have to review conduct throughout the trial period.

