### Statistical analysis

The analysis will be conducted on the basis of the intent-to-treat (ITT) principle. Some descriptive analysis of the data gathered during each assessment will be carried out precisely until the final assessment. Special time points for analysis are the baseline, end of iTBS or sham iTBS sessions, and 3 and 6 months after the final treatment. Median and range describe continuous variables, and frequencies and percentages describe qualitative variables.

We will accept a significance level of 5% (*P* < 0.05) corrected for multiple comparisons when needed. To assess our primary endpoint criterion, i.e., cognitive performance changes on the task, outcomes at four time points will be compared using repeated measurement analysis of variance of variance with time (baseline, ending, and 3 and 6 months after the final treatment) and group (study group (iTBS+WMT), WMS control group (iTBS+SRT), iTBS control group (sham iTBS+WMT), and placebo control (sham iTBS+SRT)) as factors. Further comparison between the two groups can show the simple iTBS effect, the simple WMT effect, and the facilitation effect of iTBS on WMT. Sensitivity analyses will explore the impact of imputation of data losses including loss to follow-up and dropout.

In the case that the data do not meet the normal distribution assumption, the non-parametric Mann-Whitney test will be used to compare performance improvements between four groups. SPM will be used to analyze imaging data to detect any changes in brain function and structure caused by cognitive training.

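### Emergency unblinding takes a patient off-trial, and the protocol nowhere preserves that patient's outcome and safety follow-up, which does not fit the intention-to-treat analysis

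*Protocol article*

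**What the plan says.** The Randomization section of the protocol article gives one ground for opening the code: "Blinding will have to be broken only if a patient needs emergency handling". The next sentence gives the consequence: "Once in this way, the participant will be managed as off-trial".

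Two other exits are described elsewhere.

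- **Dropping criteria:** a patient is dropped for worsening illness that calls for a different antipsychotic, and under a criterion about ten uncompleted training sessions.
- **Data monitoring:** after noting that "The intervention may produce mild adverse events, such as headache and irritability", and that rest or spacing of stimulation can relieve them, the section adds: "If the patients show unbearable, they can opt out of the trial". It then says: "We should report this situation to the supervisory department for record".

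On analysis, the Statistical analysis section states: "The analysis will be conducted on the basis of the intent-to-treat (ITT) principle". It also plans sensitivity analyses on the imputation of data lost through dropout and loss to follow-up. The Follow-up section schedules visits at baseline, at the end of treatment and at three and six months, supported by reminder calls. The visual analogue scale of side effects is a secondary outcome and is rated at all four time points.

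**The concern.** Opening the code in an emergency is a reason to end blinded treatment. It is not in itself a reason to stop observing the patient. If off-trial status means that assessments cease, whether a patient's later data exist depends on a safety event that occurred after randomisation and may be related to the assigned arm.

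Two comparisons are exposed. The first is efficacy: an intention-to-treat analysis of the MATRICS Consensus Cognitive Battery (MCCB) needs outcomes from everyone randomised, whatever happens to their treatment or blinding. The second is tolerability: a patient taken off trial after an emergency could be missing from the side-effect comparison of active with sham stimulation because of a tolerability problem.

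**Working it through.** The point is one of wording, so the check sets the sections side by side.

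1. **Is this a stated rule or an omission?** It is stated. Randomization names both the trigger (an emergency) and the consequence (off-trial). It is not a detail that a condensed article simply left out.
2. **Does any section say follow-up stops?** No. That is an inference from the term used, though the natural one.
3. **Does any section say follow-up continues?** No. The reminder calls in Follow-up point to the next interview, and nothing extends them to a patient who is off-trial. Dropping criteria and Data monitoring do not separate stopping the intervention from leaving follow-up.
4. **Does the analysis plan close the gap?** Only in part. Intention-to-treat keeps the patient in the assigned arm, and imputation can supply missing cognitive scores under assumptions. Those assumptions are least secure when the cause of the missing score is an emergency. Imputation cannot supply the course or outcome of an adverse event that was not observed.

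**Size.** No rate of emergency unblinding or of intolerance is given, so the expected number cannot be computed. With 200 patients allocated 1:1:1:1, each arm has 200/4 = 50 and the two active-stimulation arms have 2 × 50 = 100. Each patient lost this way is 1/50 = 2% of an arm and 1/100 = 1% of those on active stimulation.

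**Is power the issue?** No, on the protocol's own assumptions: response rates 77.2% and 41.4%, 80% power, 5% significance, taken here as two-sided. The pooled formula is

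n = [1.960·√(2·p̄·(1−p̄)) + 0.842·√(p₁(1−p₁) + p₂(1−p₂))]² / (p₁−p₂)²

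With p̄ = 0.593, this is (1.960 × 0.695 + 0.842 × 0.647)² / 0.358² ≈ 28.4, or 29 rounded up. The arcsine formula gives 28.05. The stated 28 is reproduced to within one patient. After the allowed 20% dropout, 50 × 0.80 = 40 per arm remain, with about 92% power for that difference. A few emergency removals would not change this. What matters is which patients are lost, not how many.

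**The case against.** The strongest reply is that off-trial may mean only that clinical care passes outside the trial regimen. Intention-to-treat governs analysis by assigned arm, and Randomization does not say that an unblinded patient's data are deleted. The planned sensitivity analyses show that the authors expect patients who leave to remain in the analysis. Serious-event definitions and expedited reporting normally sit in the full protocol, not in an article.

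Much of this stands, and it limits the point. The conflict is one of fit, not a flat contradiction. What remains is that a sentence which is printed reads as removal from the trial, and nothing printed counters that reading.

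A reader might infer more than the article supports:

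- **That follow-up definitely ends.** The text never says so.
- **That the patients lost are precisely those with the worst events.** The opt-out is the patient's own choice and follows a description of mild effects. A serious event that needs no unblinding is not covered by the rule in Randomization.
- **That a serious event could go unnoticed between audits.** The audit group "is responsible for regularly reviewing the progress, authenticity, and safety every 6 weeks", which matches the length of the treatment course. But the same section names a person independently responsible for data monitoring, and an independent Data Monitoring and Ethics Committee that reviews conduct throughout the trial.
- **That a report is triggered only by opting out.** The situation to be reported may equally be the intolerable effect itself, and reporting triggers are detail that an article may leave to the full protocol.

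**Conclusion.** The concern holds in a limited form. As written, the rule on emergency unblinding reads as removal from the trial because of a post-randomisation safety event, and no section preserves outcome or safety follow-up for that patient. It does not fit the intention-to-treat principle, and it can selectively remove information from the active-versus-sham comparisons.

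This rests on taking off-trial in its ordinary sense. If the full protocol defines the term as leaving the intervention only, the remaining problem is unclear wording. The number affected is unknown and probably small, and neither the size nor the direction of any bias can be derived from the article. A change is still worthwhile: the affected data bear directly on safety, and recruitment was under way when the article was written, so a clarification could still protect data.

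**What to change.** Reconcile the Randomization rule, and with it the Dropping criteria and the opt-out in Data monitoring, with the Statistical analysis section. The amended text should state that:

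- breaking the blind or stopping the intervention does not by itself end follow-up;
- the patient stays in the assigned arm for analysis;
- patients who still consent keep the scheduled post-treatment, 3-month and 6-month assessments, with raters who remain blinded;
- the outcome of the adverse event is recorded.

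Withdrawal of consent to further assessment should be recorded separately from stopping the intervention. Nothing here concerns when stimulation should be stopped, which is a clinical matter.

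The visits, blinded raters and electronic case report form already exist. The cost is a wording amendment with ethics review, and a few extra visits for patients no longer receiving the intervention.
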